**4.8 Outcomes:**

***Primary:*** The primary outcome measured will be exclusive breastfeeding at 3 months, or 3 months corrected if the infant was born prematurely. Exclusive breastfeeding is defined as no other milk intake than maternal milk. Health benefits have been demonstrated after as little as two weeks of exclusive breastfeeding50. However, a larger number of studies have reported positive health outcomes after two to four months of exclusive breastfeeding27, 50-52. Exclusive breastfeeding was chosen as primary outcome as it is a quantifiable measure. Partial breastfeeding is more difficult to define as it may range from very little breastfeeding to almost exclusive breastfeeding, which would have an impact on the magnitude of benefits imparted by breastfeeding. Breastfed babies will be defined as babies who receive no other milk than breast milk, whether directly from the breast or as expressed breast milk.

***Secondary:*** All measurements will be collected at corrected age if infant was born prematurely. 1) Exclusive breastfeeding at six months; 2) Partial breastfeeding at three months; 3) Partial breastfeeding at six months; 4) Number of re-hospitalization for jaundice in the first six months of life; 5) Number of re-hospitalization for non-jaundice related causes in the first six months of life; 6) Number of physician encounters in first 6 months of life; 7) Number of mothers seeking breastfeeding help; 8) Amount and type of breastfeeding support given by child’s primary physician in first six months of life

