# 4. RESEARCH DESIGN

**4.1 Trial Design:** This will be a randomized controlled trial with a qualitative component. Blinding of the participants in each study group will not be feasible, as the intervention group will receive counseling from a lactation consultant and the control group will not. The investigators, data analyst, and research assistant completing study follow-up will be blinded to group assignment.

**4.2 Population:** Mothers of all breastfeeding infants admitted to the inpatient units of the Children’s Hospital of Eastern Ontario (CHEO) with jaundice will be considered for this study. CHEO is a tertiary care centre that provides pediatric care to a population of 1.5 million people.

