**4.6 Study Interventions**

***Intervention group***

Mothers randomized to the intervention group will meet with an International Board of Lactation Consultant Examiners (IBLCE)-certified lactation consultant once during the infant’s hospitalization. The lactation consultant’s intervention will be based on established clinical practice guidelines48 (Appendix 3). The lactation consultant will review the benefits of breastfeeding with the mother. Assessment of breastfeeding techniques will be performed, and corrected as necessary. Mothers will be taught how to use a breast pump if the lactation consultant feels a breast pump is necessary, and specific guidelines as to when to use the pump will be discussed. Mothers will also be instructed on how to safely store their breast milk for later use. Breast pumps are already available in the hospital for breastfeeding women. Breast pumps, containers for milk storage, bottles and nipples will be provided to women who need them at no cost. Breast pumps will be loaned for a period of 6 weeks, after which the pumps will have to be returned.

Once the infant has been discharged from the hospital, the lactation consultant will offer three weekly half-hour follow-up sessions at the Children’s Hospital of Eastern Ontario (CHEO) (see Appendix 3 for further details ). The follow-up sessions will be available during day and evening hours. At every follow-up visit, the baby will be weighed on the same scale to aid in assessment of feeding difficulties. Breastfeeding techniques will again be reviewed and corrected as necessary, and the mother’s questions or concerns will be addressed. In the event that a problem is noted, such as weight loss, jaundice, decreased arousal, or any other symptom that is of concern to the lactation consultant, the child will be sent to the emergency department if urgent intervention is needed and the PI will be notified within 24 hours. The lactation consultant will keep a file for each patient, in which she will document the details of each encounter.

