**4.7 Study Measurements:**

Baseline information about the infant and the infant’s mother will be recorded at the time of study enrollment. Information about the mother will include language spoken (French or English), maternal age, number of children prior to the participating infant, number of previously breastfed children, maternal education level, household income, marital status, maternal smoking history during pregnancy and after delivery, type of health care provider who followed the pregnancy, attendance at pre-natal classes. Information about the infant will include age, birth weight, gestational age at birth, weight on admission, weight on discharge, need for IV therapy during the hospitalization, septic work up done on admission, antibiotic treatment, length of stay, and the need for formula supplementation before admission, as well as during hospital stay (see Appendix 6).

Follow-up measurements will be collected until the infant is six months of age. Mothers will be given a booklet upon discharge from the hospital, where they will be asked to record the information on formula introduction, solid food introduction, timing of return to work, number of daily formula feeds and sessions at the breast at different points in time, number of hospitalizations and reason, number of visits to primary care physicians and reason, discussion with primary care physician regarding breastfeeding, number of visits to breastfeeding support (see Appendix 6).

A second research assistant, blinded to group allocation, will phone the participating mothers 1 week after discharge from the hospital to remind them to fill out their booklet, and to collect information regarding breastfeeding and formula feeding. Other phone calls will be placed again when the infant is 2, 3, 4 and 6 months old, to remind the mothers to fill out their booklets. The research assistant will also collect the same information the women are asked to record in their booklet, as a back up method in case the booklets are lost or not appropriately filled out. The research assistant will also remind the families, at the beginning of the phone call, not to disclose whether they were allocated to the control or to the study group so that the research assistant can remain blinded.

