# 5. ANALYSIS

**5.1 Sample size:**

In our previous study of infants hospitalized for jaundice, the rate of exclusive breastfeeding at 3 months was roughly 50%17. However, we expect that rate to be lower given the reasons stated above (high level of education in the study population). Moreover, higher levels of education have been shown to be associated with higher rates of participation in different types of study53-55, making the selection bias hypothesis even more likely. Nevertheless, to be conservative we picked 50% as the rate of exclusive breastfeeding at 3 months.

Based on a systematic review of interventions to promote breastfeeding, a 25% increase in the rate of breastfeeding at 3 months is plausible18. In that meta-analysis of randomized controlled trials combining educational and support programs, breastfeeding rates in the short term increased by 36% (95% CI 22-49%), putting our 25% increase estimate at the low end of the confidence interval. This would result in an additional one in four women breastfeeding. An informal survey of hospital based consultant pediatricians confirms this as a clinically significant increase. Setting the probability of type I error at 0.05, a sample size of 58 mothers per group would result in a power of 80% to detect such an increase.

The anticipated number of patients lost to follow-up for the primary outcome is low given that our population of interest consists of young infants. Previous studies in such young children conducted at CHEO have high follow-up rates when primary outcomes were determined through phone follow-up56,57. As a result, we expect a loss to follow-up of no more than 7.5%. To account for this, we would therefore need to recruit 62 patients in each group (Appendix 9).

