**5.2 Quantitative Data Analysis**

Baseline characteristics of the study participants will be summarized using descriptive statistics. Continuous variables will be summarized using the mean, median, standard deviation, interquartile range, and range. Discrete variables will be summarized using frequencies and percentages.

The primary analysis will be a comparison between groups of breastfeeding rates at 3 months using Fisher's exact test. All tests will be two-sided, with p-values less than 0.05 taken to be statistically significant. Time to discontinuation of breastfeeding will also be compared between groups graphically using Kaplan-Meier curves, and statistically using the logrank test. Mothers still breastfeeding at the time of data collection will be treated as censored observations. The rates of breastfeeding failure (defined as discontinuation of breastfeeding before the infant is 6 months old) will be compared between mothers of infants admitted to the hospital with jaundice and randomized to the control group, and those in the community as per the breastfeeding rates determined by the Infant Care Survey37 using Pearson’s chi-squared test. Poisson regression models will be used to compare the number of re-hospitalizations for jaundice, hospitalizations for non-jaundice related causes, as well as physician encounters (emergency room visits, community pediatricians / family physicians) in both groups of patients throughout their first 6 months of life. Fisher’s exact test will be used to compare the proportion of mothers in each group seeking breastfeeding help once discharged from the hospital.

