**Follow-up sessions:**

- Same as initial consultation
- Weigh baby
- Refer appropriately if concerns arise regarding baby’s health

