**Appendix 4**

**Parent Diary**

**Patient Study Number: _________**

Please use this diary to record the types and amounts of food you have given your baby, the medical attention your baby has required, and the breastfeeding advice and help you have received.

This information should be recorded at the following times:

- one week after discharge from hospital
- when your baby is 2 months old
- when your baby is 4 months old
- when your baby is 6 months old

A research assistant will call you at these times to remind you to complete this diary. She will also ask you the same questions.

**REMEMBER**, please DO NOT disclose to this research assistant which study group you were assigned to (Lactation Consultant or Standard Care).

At the end of the study, please mail this diary back to:

Research Coordinator – Breastfeeding Study

[name]

Children's Hospital of Eastern Ontario

Department of Pediatrics

[name]

Ottawa, Ontario

[name]

If you have questions, please contact:

___________________, Research Coordinator, Breastfeeding Study

[contact] x______

[contact]

**Please complete 1 week post-hospital discharge:** ___________________ (date)

**Please record the types and quantities of food sources your child has been given or is currently receiving (please check and complete all sections that apply):**

□ *Breast Milk*

□ Currently, my child feeds at the breast an average of ____ times per 24 hour period. Each feeding lasts approximately ____ minutes.

□ Currently, my child receives expressed breast milk ____ times per 24 hour period. Each feeding is approximately ____ mL or ____ ounces.

□ My child is exclusively breast fed (receives only breast milk).

□ I completely stopped breastfeeding on _________________ (date)

□ *Formula*

□ I introduced my baby to formula on ________________ (date)

□ Currently, my child receives formula an average of ____ times per 24 hour period. Each feeding is approximately ____ mL or ____ ounces.

□ I stopped all formula on _________________ (date)

□ *Other milk (cow’s milk, soy milk, rice milk, goat’s milk, etc.)*

□ I introduced my baby to other milk on ________________ (date)

□ Currently, my child receives other milk an average of ____ times per 24 hour period. Each feeding is approximately ____ mL or ____ ounces.

□ I stopped all other milk on _________________ (date)

□ *Solids (pabulum, cereals, other prepared foods)*

□ I introduced my baby to solids on ________________ (date)

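### The 3-month primary outcome is known only from what unblinded mothers say, only one arm is counselled on the benefits of breastfeeding, and the 3-month record should be built on neutral intake counts

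*Protocol*

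**What the plan says.** - **Outcome.** Section 4.8 sets the primary outcome as exclusive breastfeeding at 3 months (corrected age if premature), meaning no milk other than maternal milk. It adds: "Exclusive breastfeeding was chosen as primary outcome as it is a quantifiable measure". The next sentence contrasts this with partial breastfeeding, which is harder to define.
- **Who knows the allocation.** Section 4.1: "Blinding of the participants in each study group will not be feasible". The follow-up research assistant is blinded, and mothers are asked not to reveal their group (4.7, Appendix 4).
- **What only the intervention arm receives.** Section 4.6: "The lactation consultant will review the benefits of breastfeeding with the mother". This happens once in hospital, and three weekly sessions are then offered. Appendix 3 lists the benefits of breastfeeding among the initial education topics and describes the follow-up sessions as "Same as initial consultation". That makes up to four exposures. The control arm has no standard breastfeeding support.
- **How the outcome is recorded.** Mothers keep a booklet and are phoned. Section 4.7: "The research assistant will also collect the same information the women are asked to record in their booklet". Each booklet page (Appendix 4) opens with a breast-milk block containing the tick box "My child is exclusively breast fed (receives only breast milk". Formula and other milk follow, each with a start date, feeds per 24 hours and a stop date.
- **When.** Sections 4.7 and 6.1 plan calls at 1 week after discharge and at 2, 3, 4 and 6 months. Appendix 4 has pages for 1 week and 2, 4 and 6 months only, and tells mothers that the calls come at those times.

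**The concern.** The person who supplies the primary outcome is the mother, not the caller. She knows her group. In one arm she has been told up to four times why breastfeeding is good, by a consultant working for the study. If that makes her readier to say that she breastfeeds exclusively, the error falls mainly in one arm and pushes the comparison towards the intervention. A blinded caller removes the caller's bias and leaves the mother's.

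The way the question is put adds to this. If the caller follows the booklet's order, the mother meets the label of exclusive breastfeeding before she is asked how many formula feeds the infant had. At 3 months there is no diary page, so no written record from that date can be compared with what she says on the phone.

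Section 8 says that the result should show whether paediatric hospitals need lactation specialists. A difference in what mothers say could be read as a difference in what infants are fed.

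**Working it through.** **Inputs from the protocol.** Type I error 0.05 and 80% power (5.1); two-sided tests ("All tests will be two-sided, with p-values less than 0.05 taken to be statistically significant", 5.2); Fisher's exact test for the primary comparison (5.2); 50% control rate and 25-point effect (5.1); control rates of 30% and 40% also considered (Appendix 9); 62 recruited per arm and 7.5% loss (5.1).

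**The plan's own figure.** Section 5.1: "Setting the probability of type I error at 0.05, a sample size of 58 mothers per group would result in a power of 80" per cent. For 50% v 75%, with pooled rate 0.625:

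n = [1.96 × √(2 × 0.625 × 0.375) + 0.8416 × √(0.5 × 0.5 + 0.75 × 0.25)]² / 0.25² = (1.342 + 0.557)² / 0.0625 = 57.7, rounded up to 58. The stated figure reproduces.

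**Evaluable mothers.** 62 × (1 − 0.075) = 57.35, so 57 per arm.

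**Assumption, not in the documents.** The true rate p is equal in both arms. A share m of the mothers who are not exclusively breastfeeding say that they are: m_I in the intervention arm and m_C in the control arm. Then

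reported rate = p + (1 − p) × m, and spurious difference = (1 − p) × (m_I − m_C).

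The chance of p<0.05 in either direction is the exact sum, over all pairs of counts out of 57, of the binomial probabilities of pairs for which the two-sided Fisher test gives p<0.05. With no over-reporting and p = 50% it is 3.1%.

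| True rate, both arms | Control over-reporting | m_I = 10% | m_I = 20% | m_I = 30% |
|---|---|---|---|---|
| 50% | none | 55% v 50%: 5.5% | 60% v 50%: 13.7% | 65% v 50%: 29.0% |
| 40% | none | 46% v 40%: 6.6% | 52% v 40%: 19.0% | 58% v 40%: 40.9% |
| 30% | none | 37% v 30%: 8.8% | 44% v 30%: 26.7% | 51% v 30%: 54.8% |
| 50% | half of m_I | 55% v 52.5%: 3.6% | 60% v 55%: 5.4% | 65% v 57.5%: 8.9% |

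Each cell gives the reported rates (intervention v control), then the chance of p<0.05. Three further checks at 58 per arm:

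- With p = 50% and accurate control reports, m_I = 15% gives 9.2% and m_I = 20% gives 14.3%. Nearly all of this favours the intervention.
- Equal over-reporting of 20% in both arms leaves the chance at 3.1%. Only a difference between arms matters.
- From an even 29/58 v 29/58, significance first appears at 41/58 v 29/58. That is 12 false reports among 29 non-exclusive mothers, or 12/29 = 41%.

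**The case against.** The strongest reply is that this is an ordinary limit of a behavioural trial that cannot be blinded, and that the protocol already has an intake-based definition and a blinded collector. Several parts of that reply stand.

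- A reader might infer that the outcome is not tied to intake at all. It is: 4.8 states the definition twice in terms of other milk. An infant recorded as taking formula at 3 months fails it whatever box is ticked.
- A reader might take the word for quantifiable in 4.8 as a promise to derive the outcome from feed counts. In context it only contrasts a clear yes/no state with partial breastfeeding.
- A reader might suppose that the tick box decides the primary outcome. No box is completed at 3 months, because there is no page. What matters is that the call repeats the booklet's items.
- Control mothers may also feel pressure to report well. All consented to a breastfeeding trial, 5.4 calls this population motivated, nurses may advise them (4.6), and 57% of the earlier cohort sought help after discharge (2.5). The counselling also ends with the third weekly session after discharge, before the 3-month call for most infants. The calculation with accurate control reports is therefore the worst case at each level.
- Field-level derivation is often left to the SAP, and the same mother supplies the counts and dates, so the remedy is partial.

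What remains is that an SAP cannot restore question order, neutral wording, a recall period or a missing diary page once the calls have been made. These belong in the protocol.

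**Conclusion.** The point holds as a cheap improvement to data collection. The direction of the possible bias is clear, and caller blinding does not address it. Its size is unknown, because no over-reporting rate is given in the documents.

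A reader might infer that modest over-reporting is enough to create a false-positive result. The figures do not support that at the planned 50% rate: 10% over-reporting in one arm gives 5.5%, about the nominal level. Material inflation there needs about 15–20% or more, mostly in one arm. If controls over-report half as often, even 30% gives only 8.9%. The threshold is lower if the true rate is lower, which 5.1 itself expects: at 30%, one-sided over-reporting of 10% already gives 8.8%, and 20% gives 26.7%.

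Below those levels the estimate is still shifted. At a 50% rate with accurate control reports, 10% over-reporting adds 0.5 × 0.10 = 5 points to the estimated difference. All figures assume no true effect, 57 evaluable mothers per arm and the planned Fisher test.

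**What to change.** In 4.7, 4.8 and Appendix 4, for both arms alike:

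1. Add a 3-month diary page, at corrected age where 4.8 requires it, and add 3 months to the times listed at the front of the diary.
2. At the 3-month call, ask for the number of formula feeds and other-milk feeds first, in neutral wording and with one stated recall period, before any question that uses the exclusive label.
3. Score the infant as exclusively breastfed only if both counts are zero.
4. Count the infant as not exclusive if the dated formula or other-milk items, including those on the 4-month page, show such milk being given at 3 months.

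A tipping-point analysis, showing how many intervention mothers would have to be reclassified for significance to be lost, is an optional supportive addition.

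The cost is one diary page, a few lines of call script and a scoring rule. There is no new visit and no change in sample size, and the cross-check uses items already collected. The downside is that observed exclusive rates may fall slightly in both arms. Because the same mother supplies the counts and the dates, the bias is reduced and not removed.

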# 5. ANALYSIS

**5.1 Sample size:**

In our previous study of infants hospitalized for jaundice, the rate of exclusive breastfeeding at 3 months was roughly 50%17. However, we expect that rate to be lower given the reasons stated above (high level of education in the study population). Moreover, higher levels of education have been shown to be associated with higher rates of participation in different types of study53-55, making the selection bias hypothesis even more likely. Nevertheless, to be conservative we picked 50% as the rate of exclusive breastfeeding at 3 months.

Based on a systematic review of interventions to promote breastfeeding, a 25% increase in the rate of breastfeeding at 3 months is plausible18. In that meta-analysis of randomized controlled trials combining educational and support programs, breastfeeding rates in the short term increased by 36% (95% CI 22-49%), putting our 25% increase estimate at the low end of the confidence interval. This would result in an additional one in four women breastfeeding. An informal survey of hospital based consultant pediatricians confirms this as a clinically significant increase. Setting the probability of type I error at 0.05, a sample size of 58 mothers per group would result in a power of 80% to detect such an increase.

The anticipated number of patients lost to follow-up for the primary outcome is low given that our population of interest consists of young infants. Previous studies in such young children conducted at CHEO have high follow-up rates when primary outcomes were determined through phone follow-up56,57. As a result, we expect a loss to follow-up of no more than 7.5%. To account for this, we would therefore need to recruit 62 patients in each group (Appendix 9).

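### The 50% control rate is called conservative, but at the 25-point design effect it needs the fewest mothers of the three rates in Appendix 9

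*Protocol*

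**What the plan says.** Section 5.1 takes the control rate from the investigators' earlier survey, where exclusive breastfeeding at 3 months was about 50%. It then states: "However, we expect that rate to be lower given the reasons stated above", the reason being the high education level of those respondents, and adds that selection bias makes this more likely. It nevertheless concludes: "Nevertheless, to be conservative we picked 50% as the rate of exclusive breastfeeding at 3 months".

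The effect is a 25% increase, explained as follows: "This would result in an additional one in four women breastfeeding". This makes it an absolute difference, 50% against 75%. The resulting claim is that "a sample size of 58 mothers per group would result in a power of 80% to detect such an increase". Loss to follow-up is put at no more than 7.5%, which leads to 62 recruited per group. Section 5.1 cites Appendix 9, a sensitivity table for three control rates and three effects. Section 5.2 names Fisher's exact test for the primary comparison and sets the level: "All tests will be two-sided, with p-values less than 0.05 taken to be statistically significant".

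**The concern.** In a sample-size section, calling an assumption conservative tells the reader that it errs towards a larger trial, so that the stated power should hold or improve if the assumption is wrong. Here the protocol expects the truth to lie on one particular side of 50%, the lower side. For a fixed absolute difference, the variance is largest when the two rates lie symmetrically about 50%, which for 25 points means a control rate of 37.5%. Moving down from 50% therefore first raises the required number. The protocol's own appendix shows this in the rows for the design effect.

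What is at stake is the meaning of the 80%. A reader who accepts the wording takes it as a floor. Over much of the range that the investigators have in mind, it is the best case.

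**Working it through.** **Inputs.** Two-sided level 0.05 (sections 5.1 and 5.2), power 80%, control rate 50%, absolute increase 25 points, equal groups, loss 7.5% (all section 5.1). Alternative control rates of 30% and 40% come from Appendix 9. Section 5.1 gives no figure for the rate it expects, so these two are used as the illustrative range.

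**Formula.** Pooled-variance normal approximation without continuity correction:

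n = [1.960·√(2p̄(1−p̄)) + 0.8416·√(p₁(1−p₁) + p₂(1−p₂))]² / (p₂−p₁)², with p̄ = (p₁+p₂)/2.

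**Reproducing the plan's figure, 50% against 75%.** p̄ = 0.625, √0.46875 = 0.6847, √0.4375 = 0.6614. Then n = (1.960 × 0.6847 + 0.8416 × 0.6614)² / 0.0625 = 57.7, rounded up to 58. The same formula reproduces all nine cells of Appendix 9: 163, 61, 31; 173, 62, 31; 170, 58, 27. The arithmetic of the table is sound.

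**Other control rates, same 25-point effect.**

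| Control rate | Intervention rate | n per group, unrounded | Appendix 9 |
|---|---|---|---|
| 25% | 50% | 57.7 | not tabulated |
| 30% | 55% | 60.2 | 61 |
| 37.5% | 62.5% | 61.6 (maximum) | not tabulated |
| 40% | 65% | 61.4 | 62 |
| 50% | 75% | 57.7 | 58 |

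The requirement is symmetric about 37.5%, so every control rate strictly between 25% and 50% needs more mothers than 50% does. Below 25% it needs fewer: at 20%, n is 53.9.

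**Power on the sizing basis.** Power = Φ{[0.25·√n − 1.960·√(2p̄(1−p̄))] / √(p₁(1−p₁) + p₂(1−p₂))}.

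**Evaluable number.** 62 × (1 − 0.075) = 57.35, so about 57 per group. (Inflating 58 gives 58/0.925 = 62.7, which rounds up to 63. The protocol's 62 is one short, which explains 57 instead of 58 and has nothing to do with the control rate.)

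| Control rate | Chi-squared, n = 58 | Chi-squared, n = 57 | Fisher exact, n = 57 |
|---|---|---|---|
| 30% | 78.5% | 77.8% | 71.0% |
| 40% | 77.6% | 76.9% | 70.5% |
| 50% | 80.2% | 79.5% | 73.2% |

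The Fisher column sums the binomial probabilities of all tables with a two-sided p-value below 0.05.

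**Separating the causes.** Reading down a column gives the effect of the control rate: at most 80.2 − 77.6 = 2.6 points at 58 per group. Reading across the 50% row gives the other two effects: 0.7 points from having 57 instead of 58, and 79.5 − 73.2 = 6.3 points from analysing with Fisher's exact test a trial sized on the chi-squared approximation.

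**The case against.** The strongest defence has four parts.

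- **The sensitivity is disclosed.** Appendix 9 prints the larger numbers and section 5.1 cites it. That is true, and it limits the harm, but the text still draws the opposite conclusion from the table.
- **The effect is small.** It is at most four evaluable mothers per group and under three power points. The 7.5% loss is also stated as an upper limit. If all 62 per group were followed, chi-squared power would be 81.2%, 80.4% and 82.8% at 30%, 40% and 50%. This stands, and it makes the point one of justification, not of design.
- **Conservatism depends on the scale.** With a constant odds ratio of 3, the requirement would be 55 at 30%, 54 at 40% and 58 at 50%, and 50% would indeed be the cautious choice. However, the protocol states its effect as an absolute increase throughout and uses no odds ratio.
- **The pattern is not universal.** At the 15-point effect, Appendix 9 requires 163 at 30% and 170 at 50%, so 50% is not the smallest there. The point must be confined to the 25-point design effect. Even so, 50% is not the most demanding rate at any tabulated effect (at 15 points that is 40%, with 173).

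Two stronger readings are tempting. A reader might infer that any control rate below 50% leaves the trial short of 80%. Section 5.1 says only that the rate should be lower, without a figure, and the shortfall ends at about 25%. A reader might also blame the 50% assumption for power near 70%. Most of that fall comes from the mismatch between sizing and primary test, and it is present at 50% too.

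**Conclusion.** The description of 50% as conservative is wrong at the design effect. Of the three tabulated rates it requires the fewest mothers (58, against 62 and 61), and the protocol itself expects the rate to move in the direction that, down to about 25%, raises the requirement. The cost is 2 to 3 power points on the basis used for sizing. The conclusion assumes a fixed 25-point absolute increase, equal groups and a control rate between about 25% and 50%. It does not show that the sample size was miscalculated, since 58 reproduces exactly, or that the trial is seriously underpowered because of this choice. It does show that 80% cannot be read as a lower bound.

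**What to change.** In section 5.1, delete the claim of conservatism and state that 80% is not a lower bound. Add the power for control rates of 30%, 40% and 50% at about 57 evaluable mothers per group: 77.8%, 76.9% and 79.5% on the chi-squared basis, and 71.0%, 70.5% and 73.2% for Fisher's exact test. Note beside the second set that the gap between the two reflects the test mismatch, to be dealt with separately.

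Two statements should be avoided in the rewording. One is that the planned size reaches 80% near a 50% control rate: at 57 evaluable it gives 79.5% or 73.2%. The other is that 62 evaluable per group is enough for the planned test. That figure is the chi-squared requirement at 40%, and with Fisher's exact test it gives only about 77% to 78%. It should also not be confused with the protocol's 62, which is the number recruited.

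The cost is wording and a slightly less favourable stated power. Correcting the claim needs no extra enrolment.

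### The 80% power stated for 58 mothers per group belongs to an uncorrected chi-squared test; the planned Fisher's exact test has about 74% there, and about 73 to 78% depending on losses and balance

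*Protocol*

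**What the plan says.** Protocol section 5.1 sets the inputs and the result. On the control rate: "to be conservative we picked 50% as the rate of exclusive breastfeeding at 3 months". On the effect: "a 25% increase in the rate of breastfeeding at 3 months is plausible", which the text then explains as an absolute difference: "This would result in an additional one in four women breastfeeding". The comparison is therefore 50% versus 75%. The error level is given by the words "Setting the probability of type I error at 0.05". The claim that rests on these inputs is that "a sample size of 58 mothers per group would result in a power of 80% to detect such an increase". The section does not name the test behind the calculation. For losses of at most 7.5% it concludes that "we would therefore need to recruit 62 patients in each group". Appendix 9 repeats 58 for the 50%/25% row and gives eight other combinations.

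Section 5.2 names Fisher's exact test as the primary test, in the sentence that begins "The primary analysis will be a comparison between groups of breastfeeding rates at 3 months using". On sidedness and level the same section says: "All tests will be two-sided, with p-values less than 0.05 taken to be statistically significant".

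**The concern.** The sample size and the primary test are both fixed in the Protocol, one section apart, and they do not belong together. Fisher's exact test conditions on the margins and is conservative at this size, so it needs more participants than an uncorrected chi-squared test for the same power. If 58 was derived for the chi-squared test, the 80% is not the power of the analysis that will be run.

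What is at stake is the formal justification for the size of a single-centre trial of 124 mothers with one primary comparison. A power overstated by several points understates the risk of a negative result when the planned effect is real. The question cannot be left to an analysis plan, because the Protocol itself states both the power and the test.

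**Working it through.** **Inputs.** Control rate 0.50, intervention rate 0.75, type I error 0.05, power 80%, loss up to 7.5% (all section 5.1); two-sided testing with Fisher's exact test (section 5.2); equal allocation (62 in each group, section 5.1).

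**Step 1: reproduce the plan's figure.** Pooled normal approximation without continuity correction, mean rate (0.50 + 0.75)/2 = 0.625:

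n = [1.96 × √(2 × 0.625 × 0.375) + 0.8416 × √(0.50 × 0.50 + 0.75 × 0.25)]² / 0.25² = 57.7, rounded up to 58.

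The same formula gives all nine entries of Appendix 9 exactly: 163, 61, 31, 173, 62, 31, 170, 58, 27. With continuity correction, the usual approximation to Fisher's test, the 50%/25% row would be 66. The sizing method is therefore not in doubt.

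**Step 2: exact power of the test that matches the sizing.** Over all pairs of binomial counts, uncorrected chi-squared has 79.9% power at 58 per group. This is where the stated 80% comes from.

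**Step 3: exact power of the planned test.** Same enumeration, rejecting when the two-sided Fisher p-value is below 0.05:

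| Evaluable per group | Fisher power | Chance of missing the effect |
| --- | --- | --- |
| 57/57 | 73.2% | 26.8% |
| 58/58 | 74.3% | 25.7% |
| 57/58 (either way round) | 76.1 to 77.3% | 22.7 to 23.9% |
| Random 7.5% loss from 62/62, averaged | about 76% | about 24% |
| 62/62, nobody lost | 78.3% | 21.7% |
| 63/63 | 79.4% | 20.6% |
| 64/64 | 80.2% | 19.8% |

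The unused type I error explains the shortfall: the maximum true level of Fisher's test is about 3.2% at 57/57 and 58/58, 4.1% at 57/58 and 3.8% at 62/62. Power does not rise smoothly with n. It is lowest when the groups are exactly equal, and an uneven split with almost no losses can edge past 80% (the same enumeration gives 81.0% with 61 controls and 62 in the intervention group). The average is the better single summary.

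**Step 4: lower control rate.** Section 5.1 expects the true control rate to be below 50%. With the same 25-point difference from 40% or 30%, Fisher power at 58 per group is about 72%.

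**Step 5: loss allowance.** 58/(1 − 0.075) = 62.7, which rounds up to 63. Conversely 62 × 0.925 = 57.35, so about 57 remain per group if the full 7.5% is lost. The figure 62 agrees with 58 × 1.075 = 62.35 rounded down.

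**The case against.** The strongest reply is that this is a modest matter. Fisher's test is a legitimate, conservative choice that holds type I error below 5%, so nothing is biased and no false-positive risk is added. The inputs are openly approximate, and Appendix 9 shows the required size running from 27 to 173 per group across its assumptions. Against a 50% control rate, Fisher's test at 58 per group reaches 80% power at a difference of about 26.5 points instead of 25. All of this stands, and it limits how serious the point is. It does not make the stated 80% correct for the stated test.

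Two stronger readings are tempting, and the Protocol does not support them.

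- A reader might infer that the trial simply has 73 to 74% power and a 27% chance of missing the effect. That needs exactly equal groups at 57 or 58. The 7.5% is given as a ceiling, losses fall at random, and 124 × 0.925 = 114.7, or about 115 evaluable in total, cannot split evenly. About 76% is the fairer expectation.
- A reader might infer that 62 recruited leaves only 57 evaluable and that this is a main cause of the shortfall. It is the worst case within the ceiling. The slip is one mother per group and about one point of power. Correcting it to 63 would not restore 80% under Fisher's test, which has 79.4% at 63 even with no losses.

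**Conclusion.** The point holds as a mismatch between the sizing formula and the planned test. The 58 is computed correctly for an uncorrected chi-squared test, but the 80% attached to it is not the power of the Fisher's exact test named in section 5.2. For 50% versus 75% at two-sided 0.05, that test has 74.3% power at 58 per group, roughly 76% on average after 7.5% random losses from 62 per group, and 78.3% with 62 per group and no losses. The chance of missing the planned effect is about 22 to 27%, roughly 24% expected, against the 20% implied.

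These figures assume independent binomial outcomes, the stated rates and, for the average, losses unrelated to group or outcome. The validity of the primary test is not in question; what is wrong is the power claimed for it. The 62-versus-63 slip is a side note.

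**What to change.** Choose one of the following. Neither needs extra patients.

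1. **Keep Fisher's exact test** in section 5.2 and restate the power in section 5.1 as about 74% at 58 evaluable per group, and about 73 to 78% depending on losses and balance. The cost is an openly lower power.
2. **Prespecify a primary test that matches the sizing**, before any outcome data are seen, since a later move to a less conservative test would look data-driven. Boschloo's unconditional exact test gives about 79% at 57 per group with type I error kept within 5%. Uncorrected Pearson chi-squared gives 79.9% at 58 per group, but its maximum true type I error is about 5.3 to 5.9% depending on the group sizes. The cost is a change of wording in section 5.2.

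If the sponsor wants both Fisher's test and 80% power, the trial has to grow: 64 evaluable per group, or 64/0.925 = 69.2, so 70 recruited per group instead of 62.

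In every case, name in section 5.1 the test and formula behind the 58 and Appendix 9, and state that 62 recruited per group leaves about 57 evaluable if the full 7.5% is lost.
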